## Methods and design

We will randomize 32 outpatients with SCI and their caregivers to a 9 month MFG intervention (MFG-SCI, *n* = 16 pairs) or to an SCI education control condition (SCIEC, *n* = 16 pairs) of the same duration. Over time, each condition will have 4 to 5 cohorts of 3 to 5 couple pairs. Participants will receive the different treatments at a single medical rehabilitation hospital. All participants will provide written informed consent prior to participation. The SCIEC condition will be based on the 4th Edition of the book titled: *Yes, you can: A guide to self-care for persons with spinal cord injury* [25]. The content will be taken from four sections of the book and will be covered in 16 bi-monthly sessions: 1. How SCI affects your body; 2. Maximizing your function; 3. Coping and Living with SCI; and 4. Staying healthy with SCI. The study will employ a two-arm randomized intervention-control design with repeated measures of outcomes across time. Depending on characteristics of individuals with SCI who consent to participate, we will stratify participants on time since injury (≤18 months post discharge vs. 19–36 months) and location/severity of the SCI (American Spinal Injury Association [ASIA] Classification system) and randomize to the two conditions, rigorously assessing outcomes of those with SCI and their caregivers. The SCIEC intervention will provide SCI management information in a didactic format, but it will not include the group problem-solving or structured social support afforded by MFG over the same 9-month period. Each of the clinicians will be provided a manual for didactic components of the intervention; in addition, they will receive bi-weekly supervision by the PI. For all participants, we will continue to measure outcomes after completion of the 9-month intervention period in order to assess durability of outcomes.

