### Outcome measures

Individuals with SCI and their caregivers will be assessed pre- and post-treatment and 6 months post-treatment (see Table 1). Outcomes will be assessed with psychometrically validated quantitative measures for persons with SCI and caregivers. We will also measure the quality of the dyad’s relationship. Qualitative focus groups will be conducted with all participants at the end of the treatment periods to uncover participant perceptions of overall group experience, how useful it was, suggestions for improvement, and information and/or coping skills they learned to support rehabilitation or care giving.

**Table 1 Tab1:** SCI and caregiver assessments and measurement schedule

		Pre-treatment	Post-treatment	6-months
SCI Patient Assessments				
Patient Activation				
	**Patient Activation Measure (PAM)**	X	X	X
Emotion Regulation/Interpersonal Skills				
	AX Scale (anger expression)	X	X	X
	Duke Social Support Index (use of supports)	X	X	X
Mental Health/Health Behavior				
	CES-D-10 (depression)^a^	X	X	X
Neuropsychological				
	Mini-Mental Status Examination	X		
Caregiver Assessments				
Caregiver Burden/Health				
	**Caregiver Burden Inventory**	X	X	X
	**CES-D-10 (depression)** ^**a**^	X	X	X
Dyad Functioning (administered to patient and care partner)				
	F-COPES	X	X	X

Bolded measure indicates primary outcome measure

^a^covariate in analyses

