
### Tests of specific study hypotheses

Statistical analyses will test each of our a priori hypotheses that (1) MFG-SCI will be superior to SCIEC for SCI quality of life measures (patient activation, health status), and emotion regulation, caregiver burden and health status, and relationship functioning, and (2) MFG will be more effective for individuals with SCI and their caregivers when the person with SCI is within 18 months of discharge from inpatient rehabilitation compared to when the patient is between 19 and 36 months post discharge from inpatient rehabilitation. GLMM and RMANOVA will test main effects for Group, Time since Inpatient Treatment, and Time of Measurement, as well as the Group-by-Time of Measurement and Time since Inpatient Treatment-by-Time of Measurement interactions. GLMM will also be used to estimate effect sizes for each main effect.

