### Power calculations

No studies comparing MFG to a control condition in an SCI population exist from which to estimate power. Therefore, we have used a recent trial that included [name] as a co-investigator implementing MFG with survivors of TBI and their families [24]. Significant decreases were reported in TBI patient anger-expression, social support, and occupational activity, with caregivers reporting significantly decreased caregiver burden; all *p*’s < .05. Effect sizes across measures ranged from .6 to 1.0. The proposed study will be powered to determine whether the MFG-SCI is superior to the SCIEC control condition in 2 × 2 × 3, group-by-time since inpatient rehabilitation (0–18 months post-inpatient rehab vs. 19–36 months) by measurement time (baseline, post-treatment, 6-month follow-up) analyses of variance with repeated measures on the second factor. We have elected to estimate statistical power for the more conservative RMANOVA than for the more liberal GLMM procedure in order not to overestimate power. Given the lower bound effect size of .6, a 2-sided type I error rate of 0.01 [24], 1 degree-of-freedom for each between-groups comparison and 2 degrees-of-freedom for the repeated measures main effect, and an estimated correlation among repeated measures of 0.2, at a sample size per group of 16 (32 total dyads), the power to establish superiority of the intervention over the control condition is estimated to be 97 % across the primary and secondary endpoints for SCI patients and caregivers. If we were to lose four dyads to attrition, reducing number of dyads to 28 (14 per group), statistical power given the parameters above would be 95 %. Additionally, at a more conservative effect size of .5, at a sample size of 28, we would still have 87 % power to detect a main effect among groups. Thus, we have good power to detect a medium to large effect size even with a moderate degree of attrition. All power calculations were made with PASSv11.

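### None of the listed tests isolates the arm difference at 6 months, so the question of durability that later measurement is meant to answer has no matching analysis

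*Protocol article*

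**What the plan says.** In the protocol article, Methods and design gives the reason for measuring beyond the programme: "we will continue to measure outcomes after completion of the 9-month intervention period in order to assess durability of outcomes". Under Outcome measures there are three assessments: "Individuals with SCI and their caregivers will be assessed pre- and post-treatment and 6 months post-treatment". The 6-month visit is thus the only one later than the end-of-treatment assessment.

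Tests of specific study hypotheses sets out the analyses. Three main effects are to be tested by both methods, the mixed model and the repeated-measures analysis of variance. The same sentence then adds two interactions, each with the assessment visit: "as well as the Group-by-Time of Measurement and Time since Inpatient Treatment-by-Time of Measurement interactions". On estimation the section says: "GLMM will also be used to estimate effect sizes for each main effect". Neither of the two hypotheses mentions durability.

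Power calculations supplies the design values used below: "Given the lower bound effect size of .6, a 2-sided type I error rate of 0.01", and "an estimated correlation among repeated measures of 0.2", with 16 dyads per group. The power it reports is for a between-group main effect.

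**The concern.** A durability question asks whether the arms still differ at 6 months, compared with where they started. None of the listed quantities measures that difference:

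- The Group main effect is an average over pre-treatment, post-treatment and 6 months.
- The Group-by-Time test asks only whether the three arm differences are unequal. It has 2 df and no direction.
- The other main effects and the second interaction do not compare arms over time.
- Effect sizes are promised only for main effects, so the list includes no estimate at 6 months either.

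Every dyad is asked for a further assessment after the programme. If the analysis follows the list and stops there, a significant result cannot tell a lasting benefit from one that has disappeared. The choice of how to look at the 6-month data would then be made after seeing them.

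**Working it through.** **Inputs.** From Power calculations: 16 per arm (N = 32), two-sided alpha .01, a common correlation ρ = 0.2 and m = 3 measurements. The metric of the effect size .6 is not stated, so both readings are carried: d = 0.6 SD, and Cohen's f = 0.6, which for two equal groups means d = 2f = 1.2 SD. Assumptions: equal variances, and equal arm means before treatment, as randomization implies.

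**1. The plan's own figure.** For the Group main effect, λ = N f² m / (1 + (m − 1)ρ), with 1 and N − 2 df.
- N = 32, f = 0.6: λ = 32 × 0.36 × 3 / 1.4 = 24.7, power 98.3% (stated 97%).
- N = 28, f = 0.6: λ = 21.6, power 96.1% (stated 95%).
- N = 28, f = 0.5: λ = 15.0, power 85.2% (stated 87%).

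All agree within 2 points. Reading .6 as d gives 41% at N = 32. The stated power therefore belongs to a Group difference of 1.2 SD averaged over all three visits, and says nothing about Group-by-Time or about 6 months.

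**2. Group-by-Time, effect lost or kept.** Write the arm differences at the three visits as (0, d, 0) if the effect is lost by 6 months and (0, d, d) if it is fully kept. The test depends on their squared deviations from their own mean:
- Lost: mean d/3, sum (1/9 + 4/9 + 1/9)d² = (2/3)d².
- Kept: mean 2d/3, sum (4/9 + 1/9 + 1/9)d² = (2/3)d².

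λ = (n/2)(2/3)d² / (1 − ρ), with n = 16 per arm and 2 and 60 df, so λ = 8 × (2/3)d² / 0.8 = 6.67d².

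| d | λ | Power, lost | Power, kept |
|---|---|---|---|
| 0.6 | 2.40 | 9.6% | 9.6% |
| 1.0 | 6.67 | 35.8% | 35.8% |
| 1.2 | 9.60 | 54.6% | 54.6% |

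Simulation agrees to within sampling error (at d = 1.2, 54.6% lost and 54.9% kept). At an assumed ρ = 0.5 and d = 1.2 both are 81.2%. A difference that appears only at 6 months, (0, 0, d), has the same sum of squares and hence the same power.

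**3. Group main effect.** The mean arm difference over visits is d/3 if lost and 2d/3 if kept. λ = (n/2)(mean difference)² / ((1 + 2ρ)/3), with 1 and 30 df.
- d = 0.6: λ = 0.69 lost, 2.74 kept; power 3.7% and 15.6%.
- d = 1.2: λ = 2.74 lost, 10.97 kept; power 15.6% and 71.0%.

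This test does respond to persistence. But it rejects well above 1% when nothing remains at 6 months, and its estimate is a three-visit average.

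**4. A contrast that answers the question.** For the arm difference in change from pre-treatment to 6 months, the noncentrality is d / √((2/n) × 2(1 − ρ)) = d / √0.2. That is 1.34 at d = 0.6 and 2.68 at d = 1.2. With 30 df, power when the effect is kept is about 10% (d = 0.6) and 48% (d = 1.2). With the pooled 60 df it is 10.2% and 51.3%. When the effect is lost it rejects in 1%.

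**5. Fixed-order testing.** If the post-treatment contrast must pass at .01 before the 6-month one is tested, simulation of a fully kept effect at ρ = 0.2 gives durability established in about 3% of trials (d = 0.6) or 31% (d = 1.2). At ρ = 0.5 the figures are about 6% to 7% and 60%.

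**6. Unequal correlations.** The mixed model allows them, and the equality in step 2 then fails. At d = 0.6 with assumed AR(1) correlations, power for lost against kept is 10.5% and 8.4% (0.2), 22.2% and 13.1% (0.5), and 46.8% and 24.2% (0.7). In these patterns the test favours the lost effect.

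**The case against.** The strongest reply is that this is a condensed article. Following an omnibus interaction with visit-specific contrasts is commonly left to an analysis plan, and nothing in the article rules it out. That stands as a limit on scope: a reader might infer that the trial has no 6-month contrast at all, and the article does not show that. It does not remove the point, because the article itself states a purpose and then lists tests and estimates that do not serve it.

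Four further objections narrow the claim.

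- **Durability is not a hypothesis.** It is a stated purpose only, and assessing it could be descriptive. No stated power figure or error rate depends on it.
- **The data can answer the question.** A reader might conclude that the trial would be unable to say whether the effect lasts. The planned model already contains the arm difference at each visit; what is missing is a named contrast.
- **Misreading is not certain.** It is tempting to say that a significant interaction would be taken as lasting superiority. The article says nothing about how the interaction will be interpreted, so this is a risk only.
- **Equal power is conditional.** It needs equal variances and one common correlation. Without these the powers differ, although in the patterns tried the difference does not help the test detect persistence.

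**Conclusion.** The point holds as limited. Of the tests and effect sizes listed under Tests of specific study hypotheses, none isolates the arm difference at 6 months, although durability is the given reason for measuring after the programme. Under the plan's own correlation with equal variances, Group-by-Time has identical power for a lost and a fully kept effect, from 9.6% (d = 0.6) to 54.6% (d = 1.2). The identity holds at every d, so it does not depend on how .6 is read; only the level of power does. A significant interaction is therefore not evidence of durability, and neither is a significant Group main effect.

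This should be fixed, but it does not threaten the trial: neither hypothesis is a durability hypothesis, the sample size does not depend on it, and the remedy needs no new data.

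**What to change.** In Tests of specific study hypotheses, name two 1-df arm contrasts for each outcome, both from the mixed model already planned:

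1. the arm difference in change from pre-treatment to post-treatment (efficacy);
2. the arm difference in change from pre-treatment to 6 months (durability).

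Report both estimates with 99% confidence intervals, to match the .01 criterion. Base any statement about durability on the second contrast, and keep the Group-by-Time F test as a descriptive omnibus.

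The cost is wording, plus an honest statement of power. At correlation 0.2 the 6-month contrast alone has about 10% (d = 0.6) to 48% (d = 1.2) power. Testing the two in fixed order, each at .01, adds no alpha within an outcome. But it lowers the chance of establishing a fully kept effect to about 3% to 31%, and it blocks any claim for an effect that emerges only at 6 months. The ordering is therefore optional; if it is adopted, its power should be disclosed. With power this low, the interval at 6 months will be more informative than the test, and a non-significant contrast should not be reported as loss of effect.

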### Power calculations

No studies comparing MFG to a control condition in an SCI population exist from which to estimate power. Therefore, we have used a recent trial that included [name] as a co-investigator implementing MFG with survivors of TBI and their families [24]. Significant decreases were reported in TBI patient anger-expression, social support, and occupational activity, with caregivers reporting significantly decreased caregiver burden; all *p*’s < .05. Effect sizes across measures ranged from .6 to 1.0. The proposed study will be powered to determine whether the MFG-SCI is superior to the SCIEC control condition in 2 × 2 × 3, group-by-time since inpatient rehabilitation (0–18 months post-inpatient rehab vs. 19–36 months) by measurement time (baseline, post-treatment, 6-month follow-up) analyses of variance with repeated measures on the second factor. We have elected to estimate statistical power for the more conservative RMANOVA than for the more liberal GLMM procedure in order not to overestimate power. Given the lower bound effect size of .6, a 2-sided type I error rate of 0.01 [24], 1 degree-of-freedom for each between-groups comparison and 2 degrees-of-freedom for the repeated measures main effect, and an estimated correlation among repeated measures of 0.2, at a sample size per group of 16 (32 total dyads), the power to establish superiority of the intervention over the control condition is estimated to be 97 % across the primary and secondary endpoints for SCI patients and caregivers. If we were to lose four dyads to attrition, reducing number of dyads to 28 (14 per group), statistical power given the parameters above would be 95 %. Additionally, at a more conservative effect size of .5, at a sample size of 28, we would still have 87 % power to detect a main effect among groups. Thus, we have good power to detect a medium to large effect size even with a moderate degree of attrition. All power calculations were made with PASSv11.

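### The power paragraph never names its effect-size metric, and no reading makes both the stated powers (97 %, 95 %, 87 %) and the medium-to-large conclusion true

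*Protocol article*

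**What the plan says.** All of this is in the Power calculations section of the protocol article.

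- **Source of the effect.** A trial of the multi-family group intervention in traumatic brain injury is used as the basis: "Effect sizes across measures ranged from .6 to 1.0". The section does not say whether these are d or f, or whether they compare arms or compare before with after.
- **Base case.** "Given the lower bound effect size of .6, a 2-sided type I error rate of 0.01", with "1 degree-of-freedom for each between-groups comparison and 2 degrees-of-freedom for the repeated measures main effect" and "an estimated correlation among repeated measures of 0.2". The measurement factor is "measurement time (baseline, post-treatment, 6-month follow-up", so there are three visits. With 16 dyads per arm the stated power is 97 %.
- **Attrition case.** With 28 dyads (14 per arm) and the same effect, 95 %.
- **Smaller effect.** "at a more conservative effect size of .5, at a sample size of 28", 87 %. Here the section says that the power is for a main effect among groups.
- **Conclusion.** "Thus, we have good power to detect a medium to large effect size even with a moderate degree of attrition".

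**The concern.** The same number means different things on the two scales. With two equal arms, f is half of d, so .6 is a difference of 0.6 SD if it is d and of 1.2 SD if it is f. In these calculations the noncentrality differs by a factor of 4 between the two.

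The wording and the figures point in opposite directions. By the usual benchmarks (.5 medium and .8 large for d; .25 medium and .40 large for f), a medium-to-large label attached to .5 and .6 fits d. The powers of 87 % to 97 % fit f.

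This paragraph is the article's only quantitative support for 32 dyads. If the effects are d, a null result would be read against a claimed power of 97 % when the power for that effect is about 41 %. If they are f, readers would believe that the trial can detect moderate effects when it was sized for differences of 1.0 SD or more.

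**Working it through.** **Inputs, all from Power calculations.** N = 32 or 28 dyads in two equal arms; m = 3 visits; correlation ρ = 0.2; two-sided α = 0.01; effect .6 or .5; between-group main effect with 1 numerator df. The section does not give the denominator df, so both N − 2 (two arms) and N − 4 (the 2 × 2 cells) are shown.

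**Formula.** For the group main effect in a repeated-measures ANOVA with equal correlations, λ = N · m · f² / (1 + (m − 1)ρ) = N · 3 · f² / 1.4. Power is the probability that a noncentral F(1, df; λ) exceeds the 1 % critical value.

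**Reading 1: the stated effects are f.** This comes closest to the plan's figures.

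| Case | λ | Power, N − 2 df | Power, N − 4 df | Stated |
|---|---|---|---|---|
| N = 32, f = .6 | 32·3·0.36/1.4 = 24.7 | 98.3 % | 98.2 % | 97 % |
| N = 28, f = .6 | 28·3·0.36/1.4 = 21.6 | 96.1 % | 95.9 % | 95 % |
| N = 28, f = .5 | 28·3·0.25/1.4 = 15.0 | 85.2 % | 84.7 % | 87 % |

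The match is within about 2 points but not exact. For two equal arms d = 2f, so these cases assume differences of 1.2, 1.2 and 1.0 SD.

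**Reading 2: the stated effects are d, so f = d/2.**

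| Case | λ | Power, N − 2 df | Power, N − 4 df | Stated |
|---|---|---|---|---|
| N = 32, d = .6 | 32·3·0.09/1.4 = 6.17 | 41.0 % | 40.6 % | 97 % |
| N = 28, d = .6 | 28·3·0.09/1.4 = 5.40 | 34.5 % | 34.1 % | 95 % |
| N = 28, d = .5 | 28·3·0.0625/1.4 = 3.75 | 22.3 % | 22.0 % | 87 % |

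**Could another d-based set-up give the stated figures?** With f = d/2, the three cases in the same order give:

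- α = 0.02 (one-sided 0.01): 52/45/31 %
- α = 0.05: 67/61/46 %
- α = 0.10: 78/73/60 %
- ρ = 0: 58/49/33 %
- 2-df within-subject or interaction test: 61/53/35 % at α = 0.01, 83/77/60 % at α = 0.05
- mean of the two post-baseline visits: 31/26/16 %
- analysis of covariance on that mean: 33/28/18 %
- doubled N: 80/73/53 % at α = 0.01, 93/90/77 % at α = 0.05

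None matches all three.

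**Across the cited range.** On the d reading at N = 32, power is about 41 % at .6, 71 % at .8, 82 % at .9 and 91 % at 1.0.

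**Detectable difference at ρ = 0.2 (N − 4 df).** With 32 dyads, 80 % power needs about 0.88 SD and 97 % needs about 1.15 SD. With 28 dyads, 80 % needs about 0.95 SD.

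**Correlation.** A higher ρ enlarges 1 + 2ρ and so lowers λ. At ρ = 0.5, an assumed value, the divisor rises from 1.4 to 2.0. Power for d = .6 at N = 32 falls to about 27 %, and the f = .5, N = 28 case falls from about 85 % to 67 %.

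**The case against.** **The exact set-up has not been recovered.** This stands. The f reading is slightly high in the first two cases and low in the third, and no choice of ρ repairs it. At N = 28, going from .6 to .5 must change λ by (.6/.5)² = 1.44 on either scale. The stated 95 % and 87 % imply λ of about 20.4 and 15.7 (N − 2 df), a ratio of 1.30, and at most 20.89/15.47 = 1.35 after rounding. A reader might infer that the figures arise only if f was entered. The documents do not support that; f is an approximate match and the best of the readings tried. One other set-up comes within about 2.5 points: the 2-df within-subject test with f taken as d/√2 gives 99/97/89 %. But it needs α = 0.05, which is not the plan's level, and a conversion that is not the one for two equal arms. At α = 0.01 it gives 94/90/72 %.

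**The metric is inferred.** This stands too. A reader might conclude that the trial's true power is 41/34/22 %. The section does not say that its effects are d, the cited trial is not available here, and the benchmarks behind the label are convention, not protocol text. Those figures are conditional on d. They also use the bottom of the cited range or below it; at d = 1.0 the power is about 91 %.

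**The correlation was never called conservative.** Correct. The section uses that word for choosing RMANOVA over the mixed model and for the effect of .5. It would be wrong to say that it makes the claim for 0.2. A value of 0.5 has no source in the document, so that calculation is a sensitivity check and not a corrected input.

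None of this rescues the paragraph, because the inconsistency between powers and conclusion appears on both readings.

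**Conclusion.** The paragraph is wrong as written, whichever metric was meant.

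- **If d:** the three powers should be about 41 %, 34 % and 22 %, a shortfall of 56, 61 and 65 points (97 − 41, 95 − 34, 87 − 22).
- **If f:** the powers are roughly right (about 98 %, 96 % and 85 %), but the trial is sized for differences of 1.0 to 1.2 SD, and the claim of good power for a medium-to-large effect misdescribes it.

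This rests on three assumptions: the power is for the group main effect over three equally correlated visits, as the section indicates; the conventional benchmarks give the label its meaning; and the alternatives tried cover the plausible set-ups. It does not show which metric the sponsor used, and it does not show that 32 dyads is the wrong number.

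**What to change.** Rewrite the power paragraph:

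1. Name the effect-size metric and state the assumed between-arm difference in SD units.
2. Recompute the three powers, or reconcile them with the retained software output. If .6 and .5 are d, report about 41 %, 34 % and 22 %. If they are f, say that the trial is powered for differences of 1.0 to 1.2 SD.
3. In either case replace the medium-to-large sentence with the detectable difference: at ρ = 0.2, 32 dyads give 80 % power for about 0.88 SD.
4. Show how power changes at correlations above 0.2.

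The cost is one paragraph and a short recalculation. The number of dyads, the conduct and the analysis stay as they are. Depending on the metric, either the reported powers or the description of the detectable effect becomes less favourable.
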